### Qualitative component

Sample size for the qualitative component: Purposive sampling will be used to include stakeholders involved in implementing the ***SHVASAN*** model and its beneficiaries. The participants are mentioned below (Table 3). The relevant stakeholders from the adjacent PHC will be involved to understand the routine practices and the contextual differences. The data collection will continue until the saturation is reached.

**Table 3 T3:** Stakeholders for ***SHVASAN*** model-.

Stakeholders	Role in ***SHVASAN*** implementation	Data collection methodology
Accredited social health activists (ASHAs) from implementing and non-implementing PHCs ASHA supervisors	Screening of participants aged 30 years and above, who routinely do NCD screening activities at the village level Monitoring of data collection and field visits for quality assurance	Focused group discussion In-depth interviews
Participants aged 30 years and above	Beneficiaries of timely screening and diagnosis of COPD/Asthma	Focused group discussion In-depth interviews
Community health officers	Diagnosis of participants aged 30 years and above, who routinely do NCD management and diagnosis at health and wellness centres	In-depth interviews
Medical officers implementing PHCs and in non-implementing PHCs	Diagnosis and management of cases visiting the primary health centre/ referrals from Health and wellness centres	In-depth interviews
District Health Officer (DHO) and Block Taluka Health Officer (THO).	Administrators from health systems who share permissions facilitate smoother functioning	In-depth interviews
Local village leaders	Local facilitators for smoother implementation	In-depth interviews

Qualitative tools: the following qualitative tools will be created, validated, and used.
(a)Focus Group discussion guide for ASHAs and an in-depth interview guide for ASHA Supervisor(b)Focus Group discussion guide Participants (PEFR testing, spirometry diagnosed, spirometry non-diagnosed)(c)In-depth interview guide for CHO(d)In-depth interview guide for Medical Officer(e)In-depth interview of the local village leaders(f)In-depth interview guide for administrators, namely District Health Officer (DHO) and Block/Taluka Health Officer (THO).Quality checks for the qualitative component
Ensures data triangulation with data collection from multiple levels of stakeholders.Feeding back data, analytical categories, interpretations, and conclusions to stakeholders such as participants, ASHAs, CHOs, etc.The records of the research path are kept throughout the study, from documentation for prolonged engagement with the community and stakeholders to audio files, transcripts, and final reporting.The analytical cross-sectional component

This is to compare the proportions of newly diagnosed COPD and asthma cases among adults aged 30 years and above over one year between the implementing and the adjacent PHC using routine Health Management Information System (HMIS)data. This component will help assess whether implementing the ***SHVASAN*** model is associated with improved case detection for COPD and asthma compared to routine NCD implementation.

The data for diagnosis in implementing and non-implementing PHCs would be accessed from the Public Health Management Information System (HMIS).

Plan for analysis
Quantitative - Data will be entered in Microsoft Excel and then imported to SPSS (version 27) for Windows package (IBM SPSS Statistics for Windows, Version 25.0. Armonk, NY: IBM Corp). The proportions of categorical variables of interest (Respondents with COPD-Asthma diagnosis in both PHCs) will be compared using the Chi-Square test. Means of variables of interest (time for symptoms, diagnosis, age, severity of disease) will be compared using the independent t-test. The associations between disease proportion and PEFR and spirometry values will be determined using the chi-square test. A multivariate logistic regression analysis will be carried out to identify significant predictors using PEFR values in implementing PHCs.Qualitative analysis -Data from IDIs and focus group discussions will be transcribed and thematically analyzed, and if required, MaxQDA software may also be used. In-depth interviews and focus group interviews will be transcribed verbatim, checked, and corrected if required. The transcripts will then be thematically analyzed. The transcripts will be independently read to become familiar with the material. The notes on insights and patterns from the transcripts will be derived. Subsequently, participants and/or the guide may engage in discussion to reach a consensus on the content. Coding transcripts using code labels closely linked to the meaning of the quotes, and organizing codes with similar content into groups and themes, would generate initial themes. Groups and initial themes were then presented and discussed with the guide. Then, if suitable, the Normalisation Process Theory (NPT) (27) will be used as a theoretical lens to understand how the implementation of codes and initial themes, organized within the constructs of NPT, were reviewed before being refined and delineated into four main themes. In cases where themes overlap with more than one NPT construct, a best-fit choice will be made. The content will be finalized thematically later.The comparative analysis of data from both PHCs would be done using the chi-square test for characteristics of diagnosed cases. The number of newly diagnosed cases during the study period would be obtained from the Public Health Management Information System (HMIS)Feasibility index - Based on qualitative and quantitative data collection and analysis, the feasibility dimensions will be scored and finalized through Delphi consensus. The feasibility index may be derived from the scores and the assigned weights.

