The economic implications of delayed diagnosis and inadequate management are considerable. *Out-of-pocket expenditure for COPD in India is very high and is largely driven by hospitalization costs and drug costs* (9).The National Commission on Macroeconomics and Health (2005) estimated a substantial economic burden attributable to COPD and Asthma in India, emphasizing the need for public health approaches that move beyond hospital-based care. In resource-limited settings, this burden is likely compounded by limited access to diagnostic services, poor continuity of care, and delayed referral. Community-based screening by community health workers and early diagnosis may therefore offer an important opportunity to reduce avoidable morbidity, prevent exacerbations, improve quality of life, and may reduce long-term economic losses.

Considering the rising burden of chronic respiratory diseases, prevention and management guidelines for COPD and asthma were included in 2021 under the National Program for Prevention and Control of CVD, diabetes, cancers, and Stroke (NPCDCS) (10). It primarily focuses on non-communicable diseases (NCDs), such as diabetes and cardiovascular diseases, while underscoring the need for more targeted interventions for CRDs (10–12, 14). The NPCDCS includes screening for COPD at district hospitals but lacks comprehensive care at peripheral health centers near to patients’ home. The guideline specifically mentions the roles of primary health centers (PHCs) and Health and Wellness Centers (HWCs), ASHAs, and auxiliary nurse-midwives (ANMs) (13, 14). In many public sector settings, spirometry is available mainly at district hospitals, making confirmatory diagnosis inaccessible to suspected cases, who are often elderly persons from rural areas. This creates a critical diagnostic gap between community-level symptom recognition and facility-level confirmation.

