Health and Wellness Centre	Community Health Officer (CHOs)	Questionnaire (assessment of cough and dyspnea) mMRC Health promotion for BCC Awareness generation and prevention of risk factors with a special focus on the cessation of smoking and exposure to pollutants/allergens Follow up on patients put on treatment and ensure treatment compliance and lifestyle modifications	- Cough assessment - mMRC - CAT score, R/S examination - Spirometry testing for diagnosis - Grading of disease severity and referral to PHC - Presence of co-morbidities - History of previous exacerbation - Coordination and support for prescription via telemedicine - Counselling for non-pharmacological interventions - Counselling for inhalation techniques when diagnosed - Referral in case of severe cases
Primary healthcare level	Medical Officer	- PEFR testing - If PEF < 80% predicted + breathlessness/cough>8 weeks or history compatible with Asthma, provisional diagnosis of Asthma - Individuals with PEF>80% of predicted, with cough and or dyspnoea should be assessed for TB and managed accordingly, and be educated on cessation and not starting smoking, weight reduction, nutrition, and physical activity. Individuals with PEF>80% of predicted, without cough and or dyspnea, may be sent back to the community after providing health education and risk reduction	- Telemedicine for diagnosed cases at HWC with the help of experts - Cough assessment - mMRC - CAT score, R/S examination - Spirometry testing for diagnosis - Grading of disease severity and referral to PHC - Presence of co-morbidities - History of previous exacerbation - Coordination and support for prescription via telemedicine - Counselling for non-pharmacological interventions - Counselling for inhalation techniques when diagnosed - Referral in case of severe cases
Equipment and tools are available at various levels			
At the Community Level		Community-level assessment tool by ASHA for 30 < population No equipment	Peak flow meters with mouthpieces A comprehensive questionnaire to detect the suspected cases Pulse oximeter Stadiometers Weighing machine Placebo kit to demonstrate the inhalation technique to the diagnosed cases
At Health and wellness		No equipment A tool for cough and dyspnoea mMRC	Spirometers Peak Flow rate meters Pulse oximeter Screening tool Placebo kit to demonstrate the inhalation technique to the diagnosed cases

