
### Study setting

The study will be implemented in the Mulshi block (Figure 2), Pune district, Maharashtra. The Pune district is situated in western Maharashtra, at the foothills of the Sahyadri ranges, and exhibits marked geographical heterogeneity. It is one of the high-rainfall talukas of Pune district and is part of the western hilly region. Paud village in the block is the administrative headquarters. The public health infrastructure in Mulshi includes one rural hospital in Paud and four primary health centers in *Male,* Maan, Mutha, and Ambavane (24).

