**Figure 2 F2:**
[figure not shown]
‘***SHVASAN***’ study setting- Mulshi Block, Pune District Maharashtra, India.

The implementing site will be the *Male* PHC*,* where the ***SHVASAN*** model will be implemented and assessed for feasibility. The total population of *Male* PHC is 12,148 adults aged 30 years and above residing in 35 villages. The health care infrastructure includes eight HWCs, including one at the primary health center and one at the Paud rural hospital. An adjacent PHC from the same block, namely *Maan* PHC, will be selected as a non-implementing PHC for the secondary comparative objective. The Maan PHC is similar to Male PHC with respect to geographic, socio-demographic, cultural, environmental, and health care system context. It will continue routine providing services and will be used only to compare the proportions of newly diagnosed COPD and asthma cases among adults over a one-year study period.

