#### Secondary outcome

Secondary outcome: Facilitators and operational challenges in the Implementation of the ‘***SHVASAN***’ Model. Prevalence of COPD and Asthma in implementing PHC and in adjuvant adjacent PHC.

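### The Male–Maan comparison pools HMIS diagnoses reached by different routes, with no residence rule for cases diagnosed at Paud, so the chi-square result is hard to interpret

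*Protocol article*

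**What the plan says.** The protocol article makes the comparison of newly diagnosed COPD and asthma in adults aged 30 and over, Male against Maan over one year, a secondary objective. The analytical cross-sectional component names the source: "The data for diagnosis in implementing and non-implementing PHCs would be accessed from the Public Health Management Information System (HMIS". It also states the inference wanted, namely whether the model is "associated with improved case detection for COPD and asthma compared to routine NCD implementation". The plan for analysis compares a combined COPD-asthma diagnosis variable between the PHCs by chi-square. The Secondary outcome section calls the quantity something else: "Prevalence of COPD and Asthma in implementing PHC and in adjuvant adjacent PHC".

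In Male, Table 1 and the diagnosis proforma (Quantitative component) provide for pre- and post-bronchodilator-type paired spirometry readings at the HWC, with COPD and asthma categorised from them. Maan continues routine services (Study setting). For routine services, Table 1 lists no equipment at HWCs and a peak flow meter at the PHC, with this diagnostic step: "If PEF < 80% predicted + breathlessness/cough>8 weeks or history compatible with Asthma, provisional diagnosis of Asthma". It lists no COPD diagnosis at that level. The Introduction adds that in many public settings "spirometry is available mainly at district hospitals, making confirmatory diagnosis inaccessible to suspected cases".

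On sites, Study setting says "The public health infrastructure in Mulshi includes one rural hospital in Paud and four primary health centers in" Male, Maan, Mutha and Ambavane. It then describes Male's infrastructure as "eight HWCs, including one at the primary health center and one at the Paud rural hospital". Study design includes the HWC at the rural hospital among the diagnosing sites.

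**The concern.** Two features of the numerator differ between the PHCs for reasons other than how many residents were found to have disease.

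First, the event differs. A spirometry-classified case in Male and a provisional peak-flow label in Maan enter the same test as the same outcome. A difference then mixes better detection with different labelling, and the two diseases can be affected in opposite directions.

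Second, the catchment may differ. The only rural hospital listed for the block hosts a Male diagnosing site, and the article gives no rule for assigning a case to a PHC by residence. A Maan resident diagnosed there could be added to Male's count and, if he or she would otherwise have been diagnosed in Maan, also lost from Maan's.

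This is the study's only between-PHC evidence on case detection, and the Discussion intends the results to inform wider rollout. Under the prevalence label, readers could also take the gap as a difference in disease frequency.

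**Working it through.** **1. The plan's own figure.** The stated sample size is for a single proportion: n = z²p(1−p)/d² = 1.96² × 0.08 × 0.92 / 0.008² = 4,417.8, so 4,418; doubled, 8,836. Both figures reproduce. They concern the precision of one prevalence; the article gives no sample size for the Male–Maan comparison.

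**2. What differing routes can do.** Inputs from the article: COPD prevalence 8%, asthma 3.3% or 8.7%, and 12,148 adults in Male. Assumed: the same disease frequency and number of adults in Maan, and 10% of cases coming to diagnosis in both PHCs, so that true detection opportunity is equal. Expected Male counts:
- COPD: 12,148 × 0.08 × 0.10 = 97
- asthma: 12,148 × 0.033 × 0.10 = 40, or 12,148 × 0.087 × 0.10 = 106

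Maan's count depends on what happens to its COPD cases, which the routine pathway has no step to diagnose. P values are from the two-sided pooled test (chi-square without continuity correction).

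| Maan's COPD cases | Total, Male vs Maan | Asthma alone, Male vs Maan |
|---|---|---|
| Unrecorded | 137 vs 40 or 203 vs 106 (both p<0.001) | equal |
| Half labelled provisional asthma | 137 vs 89 (p=0.001) or 203 vs 154 (p=0.009) | 40 vs 89 (p<0.001) or 106 vs 154 (p=0.003) |
| All labelled provisional asthma | equal | 40 vs 137 or 106 vs 203 (both p<0.001) |

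In every row COPD is 97 vs 0. So COPD favours Male, asthma alone is equal or favours Maan, and the pooled total can show a large gap or none. With 5% or 20% coming to diagnosis the directions are the same; at 5%, with 8.7% asthma and half relabelled, the total is 101 vs 77 (p=0.07).

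**3. What attribution at Paud can do.** Let k be the Maan residents diagnosed at the Paud HWC and credited to Male, with Maan's denominator assumed equal to Male's.
- If they would not otherwise have been recorded in Maan, the shift is k/12,148. For k = 20: 20/12,148 = 1.6 per 1,000.
- If each is also lost from Maan's count, the shift is 2k/12,148. For k = 20: 40/12,148 = 3.3 per 1,000.

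The lower figure is the more apt for COPD, since the routine pathway may not have recorded those cases.

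**4. How many cases would matter.** Take equal true detection in both PHCs and equal denominators, and find the smallest number giving p<0.05.

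| Assumed detection | Cases per PHC | Moved from Maan to Male | Added to Male only |
|---|---|---|---|
| 0.5% | 61 | 11 | 24 |
| 1% | 121 | 16 | 33 |
| 2% | 243 | 22 | 45 |
| 4% | 486 | 30 | 62 |

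The moved cases are 18%, 13%, 9% and 6% of Maan's total. With a Maan denominator of 8,000 to 20,000 the number moved ranges from 10 to 34, and the number added only from 21 to 70. For scale, k = 20 is 33% of 61 cases or 17% of 121. The article does not say how many Maan residents use Paud.

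**The case against.** The strongest reply is that spirometry at the HWC is the intervention. The comparison asks whether the model detects more than routine care; if routine care records little COPD because it lacks spirometry, that is the contrast of interest and not an artefact. This stands for COPD detection. It does not cover counting provisional and confirmed asthma as one event, crediting another PHC's residents to Male, or calling the result prevalence.

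A reader might also infer that a large difference in favour of the model is guaranteed, with Maan's COPD count near zero by construction. The article does not support that. Table 1 gives the national guideline, not Maan's actual practice; Table 3 gives medical officers in non-implementing PHCs a diagnostic role; the Introduction says only that spirometry is mainly at district hospitals; and provisional labels can push the asthma comparison towards Maan.

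Nor does the article say that HMIS cases are tallied by facility. Male's population is defined by residence in 35 villages and inclusion requires permanent residence, which point towards a resident count. Only the HWC located at the hospital is named as a Male site, not the whole hospital, and no section shows Maan residents being diagnosed there. The attribution problem is therefore a risk left open, not an established error. Interviews with adjacent-PHC stakeholders are planned to understand contextual differences; these can describe the asymmetry but not remove it from the counts.

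**Conclusion.** The point holds as one about interpretation. A single chi-square test on combined HMIS diagnoses sets spirometry-classified cases against a routine pathway that lists only provisional asthma. Part of the COPD difference is a genuine detection effect; the distortion from differing routes favours Male for COPD and has no fixed sign for asthma, so the pooled result cannot be read as a clean measure of improved detection, and still less as prevalence.

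The Paud HWC adds a possible shift towards Male of about 1/12,148 to 2/12,148 per case, or 1.6 to 3.3 per 1,000 for 20 cases. This rests on three assumptions: Maan's denominator equals Male's, some Maan residents are diagnosed there, and those cases are credited to Male. The outcome is secondary, so the primary feasibility index is unaffected, but the wording should be changed before the HMIS data are extracted.

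**What to change.** - Count each new diagnosis by the patient's village of residence, wherever the HMIS or the facility NCD register records it.
- Report COPD and asthma separately, and within each report spirometry-confirmed and provisional diagnoses separately.
- Add a sensitivity analysis that excludes diagnoses made at the Paud rural hospital HWC.
- In the Secondary outcome section, replace prevalence with the proportion newly diagnosed, in line with the stated objective, and say that a difference will be read as recorded detection and not as disease frequency.

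No new arm or sample is needed. The cost is modest extra work at extraction to capture residence and basis of diagnosis, more if the HMIS lacks residence and registers must be consulted. The headline difference may also turn out less favourable to the model.

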### The *SHVASAN* model

The proposed structured ***SHVASAN*** model is thus conceptualized as a decentralized, primary health care-based approach for the screening and spirometry confirmation of the rural adult residents with suspected chronic respiratory diseases, namely COPD and asthma. The model is based on evidence from national guidelines that recognize the role of the primary health care platform and ASHA in the prevention and control of NCDs; the second evidence is based on the international primary care model; and the third evidence is from the Indian models of Kerala and Maharashtra. The proposed model is named ’Screening by Accredited Social Health Activist (ASHAs) and diagnosis by Community Health officers of Asthma and COPD at the primary health care System (***SHVASAN***), is therefore designed to assess the feasibility of integrating decentralized community-based screening using a pretested validated questionnaire, and peak expiratory flow assessment by trained ASHA workers, referral support within the primary health care system, and spirometry evaluation by CHO at HWC, with the help of a trained technician. By evaluating this model in a rural setting, the study aims to generate evidence that may inform scalable strategies for early detection and management of COPD and asthma.

The primary objective of the proposed study is to assess the feasibility of implementing the ‘***SHVASAN**’* model as a primary health care-based approach for screening and diagnosis of COPD and Asthma. The details of the ***SHVASAN*** model are given in Figure 1. The secondary objectives are to identify implementation facilitators and operational challenges, and to compare the proportions of newly diagnosed COPD and Asthma cases among adults aged 30 years and above between the intervention PHC and the adjacent non-intervention PHC.

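### With one implementing and one comparison PHC, the individual-level chi-square on new COPD/asthma diagnoses cannot test whether the model is associated with better detection

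*Protocol article*

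**What the plan says.** The protocol article gives the secondary objective at the end of the section on the SHVASAN model: "to compare the proportions of newly diagnosed COPD and Asthma cases among adults aged 30 years and above between the intervention PHC and the adjacent". The sentence closes by identifying the comparator as a PHC without the intervention. The analytical cross-sectional component says why: to help assess whether implementation "is associated with improved case detection for COPD and asthma compared to routine NCD implementation". The data are one year of routine HMIS records in both PHCs.

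Study setting names one implementing PHC (Male: 12,148 adults aged 30 and above, 35 villages) and one comparator: "An adjacent PHC from the same block, namely *Maan* PHC, will be selected as a non-implementing PHC for the secondary comparative objective". No adult population is given for Maan. On comparability it states: "The Maan PHC is similar to Male PHC with respect to geographic, socio-demographic, cultural, environmental, and health care system context". No figures support this. The same section says: "The public health infrastructure in Mulshi includes one rural hospital in Paud and four primary health centers in". Of the four listed there, two (Mutha and Ambavane) go unused in the comparison.

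Under Plan for analysis, the test is: "The proportions of categorical variables of interest (Respondents with COPD-Asthma diagnosis in both PHCs) will be compared using the Chi-Square test". A later sentence there repeats the chi-square for characteristics of diagnosed cases in the two PHCs. The only regression is a logistic model confined to implementing PHCs.

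**The concern.** The model is allocated to a whole PHC, and each arm has one. The chi-square treats every adult as an independent unit and has no term for how much recorded diagnoses vary from PHC to PHC for reasons unrelated to SHVASAN. That variation matters here because the outcome is a recorded diagnosis in a routine system, which depends on staffing, access to testing and recording habits.

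This is the only comparative test of case detection in the plan, and the Discussion ties successful implementation to policy recommendations and wider rollout. A small p-value could be read as support for the model when it shows only that Male and Maan differ.

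**Working it through.** **1. The plan's own figure.** n = 1.96² × 0.08 × 0.92 / 0.008² = 4,417.8, rounded up to 4,418; × 2 = 8,836. Both stated numbers reproduce. This is a precision calculation for a single proportion and does not size a two-PHC comparison. The design effect of 2 is justified by loss to follow-up and does not enter the analysis, so it gives the chi-square no allowance for clustering.

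**2. What needs no assumption.** A cluster-level comparison has (number of clusters − 2) degrees of freedom: 2 − 2 = 0. Between-PHC variance cannot be estimated, and the model and the PHC are fully confounded. A cluster-adjusted model would not change that.

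**3. Size of the problem.** Assumptions, because the article does not give these values: 12,148 adults in each PHC (Male's figure applied to Maan), routine detection proportion p of 0.1%, 1% or 2%, between-PHC coefficient of variation (CV) of 10%, 25% or 50%, and no model effect.

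- Within-PHC standard error of the difference: SE = √(2p(1−p)/12,148)
- Between-PHC SD of the difference: SD = √2 × CV × p
- Rejection rate of the nominal 5% test: 2 × [1 − Φ(1.96 × SE / √(SE² + SD²))]

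Example, p = 1%, CV = 25%: SE = 0.128 percentage points; SD = 0.354; √(SE² + SD²) = 0.376; 1.96 × 0.128 / 0.376 = 0.666; rejection rate = 0.506.

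| Routine proportion | SE (points) | CV 10% | CV 25% | CV 50% |
|---|---|---|---|---|
| 0.1% | 0.041 | 0.064 | 0.140 | 0.330 |
| 1% | 0.128 | 0.189 | 0.506 | 0.728 |
| 2% | 0.180 | 0.293 | 0.629 | 0.805 |

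**4. Smallest difference declared significant.** 1.96 × SE is about 0.25 points at p = 1% and 0.35 points at p = 2%.

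**5. Sensitivity to Maan's size.** At p = 1% and CV 25%, with SE = √(p(1−p)(1/12,148 + 1/m)), the rejection rate is 43% if m = 6,000 and 56% if m = 24,000, against 51% at equal size.

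**6. Cross-check by intracluster correlation (ICC).** Rejection rate = 2 × [1 − Φ(1.96/√DE)], with DE = 1 + (12,148 − 1) × ICC. At ICC 0.0001, DE = 2.21 and the rate is 19%. At ICC 0.001, DE = 13.15 and the rate is 59%. The first agrees with the table: CV 10% at p = 1% corresponds to ICC = CV² × p/(1−p) = 0.0001.

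**The case against.** Several points on the other side stand.

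- The study is a feasibility study, its primary outcome is the feasibility index, and this test does not enter that index. The comparison is secondary and its wording is modest: association, not effect.
- A reader might infer that any pre-existing difference between the PHCs will come out as significant. The figures do not support that. At a 1% proportion and CV 10% the test stays non-significant about 81% of the time (1 − 0.189), and differences below about 0.25 points do not reach p < 0.05.
- A reader might infer that the p-value means nothing at all. As a contrast of two fixed PHC populations it is interpretable, apart from clustering of adults within villages.
- A reader might infer that asserted similarity is the only safeguard. It is not: the Qualitative component plans to involve stakeholders from the adjacent PHC to learn about routine practice and contextual differences. Those interviews may help interpretation, but they supply no variance estimate and do not repair the test.
- The error rates rest on assumed inputs. Because spirometry is said to be mainly at district hospitals, routine PHC detection may be very low, and the inflation is then smaller (6% to 33% at 0.1%). Active screening could also produce a gain well beyond ordinary PHC variation. An assumed 3-point gain would be 3/0.707 = 4.2 between-PHC SDs of the difference at p = 1% and CV 50%.

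The last point means that a large observed difference could still be informative. It would persuade by its size against the ordinary spread between PHCs, which this plan does not measure, and not by its chi-square p-value.

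Deferral to a separate analysis plan does not answer the concern: the article itself fixes the test and the one-against-one structure.

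**Conclusion.** The concern holds for this secondary comparison. That the model and the PHC cannot be separated, and that no degrees of freedom remain for between-PHC variation, follows from the stated design alone. The chi-square p-value is therefore not valid as a test of whether the model is associated with improved detection. The size of the inflation is conditional on the assumed proportion, CV and Maan population. It runs from barely above nominal (6%) to about 80% over the range shown, and every cell exceeds 5%. Nothing else in the article repairs the test, and the stated limitations do not mention the one-against-one design. The primary outcome stands unaffected.

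**What to change.** - Do not use the chi-square p-value as evidence for the model. Report the two proportions and their difference.
- Extract HMIS new diagnoses for the 12 months before implementation as well as the study year, in both PHCs, and report the difference in change per 1,000 adults aged 30 and above.
- Where HMIS access allows, show Mutha and Ambavane for the same periods to display the ordinary spread between PHCs. The article claims similarity only for Maan, so these are context and not matched controls.
- State that the contrast is descriptive, that one PHC per arm remains a limitation, and that the before-after contrast removes only stable differences between PHCs. It has the same zero degrees of freedom at PHC level, and it adds little if baseline diagnoses are close to zero.

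Cost: revised analysis wording and one extra routine data extract, provided HMIS holds the earlier year; no new participants. The downside is a weaker comparative claim.
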